#### Secondary outcomes

Secondary outcomes will be global perceived improvement [53], health-related quality of life (EQ-5D) [36–38], sick leave, drug consumption, and healthcare utilization. Adverse events within 24 hours post-treatment will be measured at each return visit (duration and severity) with a questionnaire that we have used in a recently published study [24] and was based on the findings reported earlier [27].

#### Automated text message follow-up

The participants are followed up with automated text messages (SMSes) every week to survey the course of neck pain and pain-related disability over one year. The use of automated text messages have been shown to be a valid and cost-effective way to survey low back pain [48, 50, 54]. The questions used are as follows: 1) How much neck pain have you had on average of the past week? Enter a number between 0 (no pain) to 10 (worst pain imaginable). 2) How much has neck pain hindered work/daily activities in the past week? Enter a number between 0 (not at all) to 10 (impossible to perform this).

#### Health economic evaluation

A health economic evaluation will be done aiming to compare costs and outcome between the four treatment alternatives. Diagnosis-related groups (DRG) will be used to define the costs [55], and EQ-5D™ will be used to model the cost effectiveness [56]. As a basis for these analyses, participants will be asked to report healthcare consumption, drug consumption and sick leave days from work in the questionnaires at all follow-ups.

### Statistical analyses

The comparison of the effect between the groups statistical analyses will be performed using an “*intention to treat”* principle aimed at analyzing participants in the group to which they were originally assigned and to keep the dropouts in the assigned group no matter what the reason [57]. To estimate the impact of missing responses, sensitivity analysis for the primary outcomes will be performed using multiple imputation [58]. Changes in mean scores at follow-up compared with baseline, and differences in changes between groups will be calculated by unpaired t-test. To compare the groups regarding the dichotomized outcomes, relative risks (RR) and risk differences (RD), together with corresponding 95 % confidence intervals (CI), will be calculated. Baseline factors that differ between the treatment groups will be considered with regard to their potential confounding effect by means of Mantel Haenszel’s method [59]. If adjustment is needed, the Cox proportional Hazard model will be used.

Generalized estimating equations (GEE) will be performed to analyze the effect on the primary outcome (pain and disability) over the total follow-up time, including the automated text messages (SMSes). The GEE method extends standard regression analysis, taking into account the covariance between repeated measurements of pain and disability [60, 61].

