### Randomization procedure

Included study participants are randomly assigned by block randomization to one of four groups in block sizes of 160 (Table 3). Stratified randomization was not used. Prior to the study start, an assistant not involved in the project prepared 800 opaque, sequentially numbered sealed envelopes with cards marked; 1 (massage), 2 (exercise therapy), 3 (massage and exercise therapy) or 4 (advice) indicating one of the four treatment arms. The number sequence was attained by placing 160 (40 of each numbered fold cards) in an urn, mixing them before placing them, one at the time, into numbered opaque envelopes. Study participants are sequentially numbered by the study assistant before the initial visit, and receive the assigned set of documents, including the envelope, with the corresponding number when they come to the study center. The unmasking is performed by the therapist after the baseline B questionnaire is filled in and after the physical examination and second- step exclusions, so that the study administrator, the therapist and the study participant are blinded to the group assignment until after all study participant baseline data have been collected.

**Table 3 Tab3:** Interventions

Treatment arm	Description	Time per treatment	Number of sessions	Duration
Massage (A)	Massage will be applied to the neck, thoracic spine area, TMJ^a^ (if indicated) and chest (including the chest muscles)	30 min (in total 45 min session)	up to 6	6 weeks
Exercise therapy (B)	Self-mobilization exercise (gentle controlled movement) of the neck and shoulder joints, including neck retraction, extension, flexion, rotation, lateral bending motions, and scapular retraction) and strengthen exercises	30 min (in total 45 min session)	Up to 6	6 weeks
Massage and Exercise therapy (C)	Combination of A + B	50 min, 25 min of each (in total 60 min session)	Up to 6	6 weeks
	Massage treatment followed by physical exercise.			
Advice to stay active (D)	Support and advice on staying active and on pain coping strategies, according to guidelines and evidence-based reviews	30 min	Up to 3	6 weeks

^a^TMJ: temporomandibular joint

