### Sample size

Power analyses based on the primary outcomes have been performed to determine the sample size. A total of 600 participants indicated a power of >80 % to detect a relative risk of 1.2 to 1.3 for a clinically important improvement in pain and disability; a two-step decrease in the mean pain intensity score (CPQ; NRS 0 to 10) and a one-step decrease in mean pain-related disability score (CPQ; NRS 0 to 10) when baseline is compared to the values at follow-up. These calculations are based on the differences in effect between manual therapy and advice to stay active detected in our previous trials, which are 16 to 27 % depending on the length of the follow-up time [26, 27].

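### The primary comparisons appear to use respondents only, and multiple imputation, if run under missing at random, cannot by itself show bias from non-response that relates to outcome differently by arm

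*Protocol article*

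**What the plan says.** All of the relevant analysis text is in the Statistical analyses section of the protocol article. Groups are to be compared by intention to treat, with the aim "to keep the dropouts in the assigned group no matter what the reason". For the mean scores, "differences in changes between groups will be calculated by unpaired t-test". For the two dichotomised primary outcomes, RR and RD with 95 % confidence intervals are planned. Missing responses get one sentence: "To estimate the impact of missing responses, sensitivity analysis for the primary outcomes will be performed using multiple imputation". The imputation model, its variables and its missingness assumption are not stated.

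The same section plans generalised estimating equations (GEE) for pain and disability over the whole follow-up, including the text-message data. Those data come from a separate stream: "The participants are followed up with automated text messages (SMSes) every week", with one pain and one disability question each week for a year.

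The Sample size section gives the effect against which any bias should be judged. The trial is powered "to detect a relative risk of 1.2 to 1.3 for a clinically important improvement in pain and disability".

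**The concern.** A t-test on change, an RR and an RD each need an observed follow-up score. Imputation is named only for sensitivity and nothing else is named for non-responders, so anyone who does not return the questionnaire most naturally leaves the primary estimate. That sits awkwardly beside the intention-to-treat statement.

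The second issue is what the sensitivity analysis can reveal. Multiple imputation in its usual form assumes that, given the variables in the model, non-responders resemble responders. If that model holds little beyond what the main analysis uses, the two results will agree whether or not non-response is related to recovery. The agreement could then be read as robustness.

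Three features of this trial make arm-dependent non-response plausible:
- The Study design section states that blinding is not possible.
- The primary outcomes are self-reported questionnaires sent by email over 52 weeks.
- Contact is unequal. Table 3 gives up to 3 sessions for advice and up to 6 for each other arm, and Table 2 lists adverse-event questionnaires, the last by phone, for arms A, B and C only.

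If non-response relates to improvement differently in the advice arm than in the others, the primary RR is biased, and the direction cannot be known in advance.

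**Working it through.** **The plan's own figure.** The Sample size section says "A total of 600 participants indicated a power of" more than 80 % for RR 1.2 to 1.3, based on "differences in effect between manual therapy and advice to stay active detected in our previous trials, which are 16 to 27" %. Allocation is equal ("40 of each numbered fold cards" per block of 160), so 600 / 4 = 150 per arm. No control rate or significance level is given. Assuming two-sided 5 %, power at 150 per arm is:
- RR 1.3: 75 % at a control rate of 0.50, 85 % at 0.55.
- RR 1.2: 41 % at 0.50, 82 % at 0.70.
- A 16-point difference: about 80 % to 92 % over control rates 0.30 to 0.70.

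The stated power is therefore attainable under some control rates but cannot be confirmed. The missing-data point does not depend on it. Only the target RR is carried forward.

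**Step 1: respondents-only RR with no true effect.** Assumed inputs: true improvement 0.50 in both arms; missing share m; improvement among non-responders q, the same in both arms. The observed rate is (0.50 − m·q) / (1 − m).

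| Missing: advice / active | q | Advice observed | Active observed | RR |
|---|---|---|---|---|
| 20 % / 10 % | 0.3 | (0.50 − 0.06)/0.80 = 0.550 | (0.50 − 0.03)/0.90 = 0.522 | 0.95 |
| 20 % / 10 % | 0.7 | (0.50 − 0.14)/0.80 = 0.450 | (0.50 − 0.07)/0.90 = 0.478 | 1.06 |
| 30 % / 10 % | 0.3 | (0.50 − 0.09)/0.70 = 0.586 | 0.522 | 0.89 |
| 30 % / 10 % | 0.7 | (0.50 − 0.21)/0.70 = 0.414 | 0.478 | 1.15 |

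The true RR is 1 in every row.

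**Step 2: does missing-at-random imputation show this?** Without informative auxiliary variables, imputing within arm fills the gap at the observed rate p: (1 − m)·p + m·p = p. The estimate does not move.

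A simulation agrees (150 per arm, 20 imputations, 2,000 trials, true improvement 50 % in both arms). Response was set at 85 %, except 65 % among treated non-improvers. In closed form the treated arm's observed rate is 0.425 / (0.425 + 0.325) = 0.567, a false RD of 6.7 points. Simulated bias was 6.6 points for respondents only and 6.6 points for imputation. False-positive rates were 19.0 % and 18.5 % against a nominal 5 %.

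**Step 3: does it matter that the pattern differs by arm?** Yes. Take true rates of 50 % and 66 %, with response of 85 % in improvers and 75 % in non-improvers in both arms. The observed rates are 0.425/0.800 = 0.531 and 0.561/0.816 = 0.688. RD moves only from 16.0 to 15.6 points.

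**Step 4: what do the SMS data add?** In a second simulation (400 trials, no true effect), response in one arm depended on the unseen change score, and imputation used an auxiliary correlated with that change. Respondents-only bias was about 11 points. Bias after imputation was about 10 points at correlation 0.3, 8 at 0.6, 4 at 0.8 and 2 at 0.9. It is reduced but not removed.

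**Step 5: what does a delta adjustment add?** In the last row of the table, setting improvement among non-responders to 0.70 gives advice 0.70 × 0.414 + 0.30 × 0.70 = 0.50 and active 0.90 × 0.478 + 0.10 × 0.70 = 0.50, so RR returns to 1. Varying that value by arm shows how far non-responders must differ before the conclusion changes.

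**The case against.** The strongest reply is that the article specifies little here, and that silence is not error. It states no analysis set and no missingness assumption. Multiple imputation can be run with outcome-dependent shifts, and such detail is commonly left to a full protocol or analysis plan not shown. This stands: the conclusion about imputation is conditional on its being run under missing at random.

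A reader might infer three stronger things that the text does not support:
- **That the plan contradicts its own intention-to-treat statement.** The word dropouts may mean people who stop treatment but still answer questionnaires. Keeping them in their arm is compatible with a separate provision for missing responses.
- **That the plan promises to estimate the effect of outcome-related non-response.** It speaks only of missing responses in general, and comparing imputed with observed results is a recognised, if partial, way to assess that.
- **That imputation can show nothing.** With SMS scores in the model it can reveal, and remove, part of the bias (Step 4).

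The planned GEE also counts in the plan's favour, because it uses people who miss a questionnaire but answer other contacts. It is not presented as a missing-data check, however, and ordinary unweighted GEE does not protect against outcome-related non-response. The protocol also measures expectations and will test them as confounders. That addresses differences among those analysed, not who is missing.

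Finally, the larger illustrative figures need a wide gap in response between arms. That is fair, and nothing in the article shows such a gap will occur.

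**Conclusion.** The point holds in a limited form. As written, imputation is reserved for sensitivity and the primary t-test, RR and RD most naturally use respondents only. If the imputation assumes missing at random, no named analysis would by itself expose bias from non-response that relates to outcome differently by arm.

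The size is illustrative. The range of 0.89 to 1.15 rests on assumed missing shares of 30 % and 10 %, 50 % true improvement, and 30 % to 70 % improvement among non-responders. At its upper end the spurious excess is 0.15 / 0.20 = three quarters of the smallest effect sought. The milder case, 0.95 to 1.06, is much less serious, and a pattern common to all arms would hardly matter. The documents do not support saying that the results will be biased. They support saying that the plan could guard against this cheaply and, as described, does not clearly do so.

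**What to change.** State how non-responders enter the primary RR, RD and mean differences, and state the assumption behind the imputation. Then:

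1. Make the imputed analysis of all randomised participants the main one. Impute the continuous CPQ scores separately by arm, using baseline CPQ, CPQ at the other follow-ups and the weekly SMS pain and disability scores. Dichotomise after imputation. Table 2 gives 104 SMS answers per person against about 150 people per arm, so summarise them, for example over the weeks before each questionnaire.
2. Report the respondents-only result as supporting. Keep the GEE as planned.
3. Add a delta-adjusted imputation in which the improvement assumed for non-responders varies by arm, and report the combination at which the conclusion changes.
4. Report response by arm at weeks 7, 12, 26 and 52, so that the reader can judge which shifts are credible.

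No new data are needed. The questionnaires and text messages are already planned, with follow-up running into 2017. The cost is analysis wording, some programming and possibly wider intervals. Item 1 alone is not enough: without informative auxiliaries it gives the respondents-only answer (Step 2), and even with them some bias remains (Step 4).

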### Inclusion criteria

The inclusion criteria are participants who are ongoing neck pain (including whiplash associated disorders (WAD)) and neck pain with headache and/or radiating symptoms in the upper limbs) of subacute (30 to 90 days in duration) or long-lasting (>90 days in duration) duration. The neck pain shall be of such a nature that it is disturbing for daily activities at work and/or leisure time according to the participant in the first contact. The person shall be in the age span 18 to 70 years (Table 1).

**Table 1 Tab1:** Eligibility screening

Inclusion criteria	Exclusion criteria
Age 18 to 70 years	Not fluent in Swedish language
Current history of subacute neck pain (30 to 90 days duration) or long-lasting neck pain (>90 days) impairing daily activities at work and/or leisure time	Pain intensity <2 as a mean of three pain questions the preceding 4 weeks (Chroniq Pain Questionnaire)
Access to internet	Pain related disability <1 as a mean of three disability questions the preceding 4 weeks (Chronic Pain Questionnaire)
In possession of a smart phone	Having used a personal trainer the preceding 4 weeks
	Pregnancy
	Cancer the preceding 5 years
	Skin disorders in the painful area impeding massage therapy
	Manual therapy, massage therapy or physical therapy for the neck pain in the preceding month
	Sick leave due to surgery in the painful area
	Specific diagnosis (as for example acute prolapsed disc, spondylolisthesis, spinal fracture, spinal stenosis, or arthritis)
	Red Flags (as for example acute trauma, cancer, infection, cauda equine, osteoporosis, or vertebral fractures)
	Fever

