### Exclusion criteria

Participants are not included if any of the following criteria are present: 1) not fluent in the Swedish language; 2) mean neck pain intensity <2/10 in the preceding 4 weeks on the three pain questions from a modified version of the Chronic Pain Questionnaire (CPQ); 3) mean pain related disability <1/10 in the preceding 4 weeks on the three disability in the CPQ; 4) pregnancy; 5) cancer in the preceding 5 years; 6) skin condition or fever, which disables the massage; 7) having received treatments for the current complaint by any manual therapist (such as naprapath, chiropractor, osteopath, physiotherapist, or massage therapist); 8) having used a personal trainer during the past month; 9) not having a smart phone and access to the internet; 10) on sick leave due to surgery in the painful area; 11) specific diagnosis such as acute prolapsed disc; 12) spondylolisthesis and spinal stenosis; or 13) “red flags” (older than 55 when the pain debuted for the first time, recent trauma in the area, constant pain or pain getting worse in the night, consumption of steroids now or recently, or drug abuser) [25] (Table 1).

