### Baseline

Baseline clinical and demographic data, as well as potential prognostic factors for neck pain, are measured using two baseline questionnaires administered before medical examination, inclusion and randomization. The first baseline questionnaire (A) is completed by telephone interview a maximum of  7 days before the first visit to the study clinic by a research assistant. Study participants fill in the second baseline questionnaire (B) at the study clinic before they meet the therapist at the first visit and before the randomization. The baseline factors are sex, age, education, pain and disability in neck and back [31, 33–35], duration of neck pain, previous episodes of neck pain, health-related quality of life (EQ-5D) [36–38], psychological distress (GHQ-12) [39], smoking, physical exercise, height, weight, sick leave, physical demands at work [40] and job strain [41, 42]. An overview of the Baselines A and B assessment is presented in Table 4.

**Table 4 Tab4:** Baseline assessments

Baseline	Contains	Instruments
Baseline A (phone call maximum 7 days before first visit)		
General Information [39, 62]	Informed consent for the enrolment in the study	
	Sex	
	Housing and housing environment	
	Education	
	Occupational class [63]	
	Previous experience from massage therapy and/or personal trainer (YES/NO)	
Neck pain	Pain intensity and disability related disability in neck [35]	Chronic Pain Questionnaire
	Duration of neck pain	
	Previous episode of neck pain	
Baseline B (paper questionnaire at first visit)		
Lifestyle [36, 39]	Height and weight	
	Cigarette smoking [64]	
	Leisure time and occupational physical activity [65]	
	Physical demands at work [40, 41]	
General health	Self-rated health [66]	
	Health related quality of life [38]	EQ-5D
	Psychological distress [67]	GHQ-12
	Emotional well-being	
	Anxiety, worry, anguish [68]	
	Expectation of recovery	
	Sleeping problems [42]	
	Persistent fatigue	
Chronic diseases	Diabetes	
	Cardiovascular disease	
	Chronic obstructive pulmonary disease	
	Psoriasis	

As part of the physical examination study participants undergo a number of clinical neck tests in order to rule out cervical radiculopathies [43], to evaluate the range of motion of the cervical and thoracic spine and to assess the deep cervical muscle function [43–47]. A flow chart over the study procedure is presented in Fig. 1.

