#### Primary outcomes

The primary outcomes are pain and disability, measured by a slightly modified Chronic Pain Questionnaire (CPQ) (4-week recall period instead of 6 months) [31, 33–35] with six items on a numerical 11-point rating scale and one item on the number of disability days of pain and disability. Three items are used to rate the pain (the current pain, the worst pain experienced during the preceding 4 weeks, and an average of the pain during the preceding 4 weeks). A pain score will be constructed from the mean of these three items. Three items are used to rate disability and concern to what degree pain “interfered with your daily activities,” “changed your ability to take part in recreational, social, and family activities” and “changed your ability to work (including housework)” in the past 4 weeks. The disability score will be the mean of these three items. On the basis of these scales, two dichotomized outcomes will be defined based on what is considered to correspond to a clinically significant improvement: a two-step decrease in pain intensity and a one-step decrease in pain-related disability when baseline is compared to the values at follow-up [52].

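### The unpaired t-test on change in mean pain and disability scores is valid between arms, but less precise than adjusting for the baseline score already collected

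*Protocol article*

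**What the plan says.** All references are to the protocol article.

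- **The scores.** Primary outcomes builds two continuous scores from the modified Chronic Pain Questionnaire (CPQ): "A pain score will be constructed from the mean of these three items" and "The disability score will be the mean of these three items". It then defines two dichotomised outcomes on the same scores: "a two-step decrease in pain intensity and a one-step decrease in pain-related disability when baseline is compared to the values at follow-up".
- **The test for mean scores.** Statistical analyses states: "Changes in mean scores at follow-up compared with baseline, and differences in changes between groups will be calculated by unpaired t-test".
- **Adjustment.** The same section provides Mantel-Haenszel adjustment, and if needed a Cox model, for baseline factors found to differ between arms. It also plans GEE over the whole follow-up and names no baseline covariate there.
- **Baseline availability.** Baseline says "The first baseline questionnaire (A) is completed by telephone interview a maximum of" 7 days before the first visit, and Table 4 lists CPQ pain and disability in that questionnaire. Table 1 excludes "Pain intensity <2 as a mean of three pain questions the preceding 4 weeks", with a similar floor of 1 for disability. The baseline score is therefore needed to establish eligibility.
- **Power.** Sample size states: "A total of 600 participants indicated a power of >80 % to detect a relative risk of 1.2 to 1.3". That refers to the dichotomised improvements.

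**The concern.** A t-test on change scores subtracts the whole baseline value, which fixes the baseline coefficient at 1. Unless the true slope of follow-up on baseline is 1, this leaves variance in the comparison that a fitted coefficient would remove. Nothing else named in the section does so for a mean score. The Mantel-Haenszel and Cox provision depends on observed imbalance and suits dichotomised outcomes.

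The sentence also has two subjects, change within an arm and difference in change between arms, and taken at its word it puts both under the unpaired test. For within-arm change that ignores the pairing.

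At stake is the width of the confidence intervals for the mean-score comparisons, and a correct standard error for any within-arm change that is reported.

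**Working it through.** **The plan's own figure.** The document gives no SD, power or sample size for the t-test, so there is none to reproduce. The stated power of over 80 % belongs to the dichotomised outcomes. With 150 per arm (600/4) and an assumed two-sided 0.05, it holds for RR 1.3 if the control improvement rate is at least about 0.53, and for RR 1.2 if it is at least about 0.69. The control rate is not stated, so the figure can be neither confirmed nor refuted. It has no bearing on the analysis of mean scores.

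**Between arms.** Let s be the SD, assumed equal at baseline and follow-up, and rho the baseline to follow-up correlation (assumed, not in the document). Variance per participant:

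- Change score: 2(1 − rho)s²
- ANCOVA: (1 − rho²)s²
- Ratio, ANCOVA to change: (1 + rho)/2

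| rho | Ratio | Change-score n matching 600 by ANCOVA | ANCOVA power where change score has 80 % |
|---|---|---|---|
| 0.3 | 0.65 | 600/0.65 ≈ 920 | 93.5 % |
| 0.5 | 0.75 | 600/0.75 = 800 | 89.9 % |
| 0.6 | 0.80 | 600/0.80 = 750 | 87.9 % |

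A simulation (4000 runs, 150 per arm, no treatment effect) gave ratios of 0.67, 0.75 and 0.85 at rho 0.3, 0.5 and 0.7; the formula gives 0.65, 0.75 and 0.85. The change-score test showed no bias, and its type I error was 0.050, 0.050 and 0.052.

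**Effect of the entry floors.** Suppose the floors cut the baseline SD to a fraction k of its untruncated value. Under a linear model the slope and residual variance stay the same, so the ratio becomes

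(1 − rho²) / [(1 − rho²) + k²(1 − rho)²].

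With k = 0.8 (illustrative, since the degree of truncation is not given) and rho defined before truncation:

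- rho 0.3: 0.91/(0.91 + 0.64 × 0.49) = 0.74
- rho 0.5: 0.75/(0.75 + 0.64 × 0.25) = 0.82
- rho 0.6: 0.64/(0.64 + 0.64 × 0.16) = 0.86

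The gain shrinks but does not vanish.

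**Within arm, literal reading.** The unpaired SE divided by the paired SE is 1/√(1 − rho), which is 1.20, 1.41 and 1.58 at rho 0.3, 0.5 and 0.6. The true two-sided type I error at nominal 0.05 would be about 0.019, 0.006 and 0.002, so the error is conservative.

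**The case against.** Several points on the other side stand.

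- **The powered analysis is elsewhere.** The sample size rests on the dichotomised improvements, compared by relative risk and risk difference. ANCOVA on mean scores changes nothing there. A reader might infer that the t-test worsens the trial's stated power; the document does not support that.
- **The test is valid.** A reader might infer that chance baseline differences bias the comparison. Averaged over randomisation they do not. For a given imbalance d the estimate is shifted by (1 − rho)d in size, but this is the precision loss seen another way: 2(1 − rho) = (1 − rho²) + (1 − rho)², and the last term is the imbalance component. It should not be counted as a second harm.
- **The entry floors are not a source of bias.** Selecting on a minimum score makes regression to the mean likely, but equally in all four arms. By narrowing the baseline SD, the floors reduce the advantage of ANCOVA.
- **The within-arm charge depends on grammar.** The paragraph opens with comparisons between groups. The authors may have meant the unpaired test only for the difference in change, where it is the proper two-sample test. No primary research question asks for a within-arm test.
- **GEE is also planned for pain and disability.** Its covariates can reasonably be left to an analysis plan that is not shown, so their absence is not a finding.

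What remains is that the protocol names a specific test for the mean scores, that this test is less efficient than one using data already in hand, and that the sentence needs rewording whichever meaning was intended.

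**Conclusion.** The point holds as a free improvement in precision and a correction of wording. It does not show an invalid analysis.

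For the between-arm comparison of mean scores, ANCOVA needs about 65 % to 80 % of the variance of the planned test at correlations of 0.3 to 0.6. If truncation reduces the baseline SD to 0.8 of its original value, the range is about 74 % to 86 %. These figures assume a linear relation and equal SDs (before truncation in the second case), and correlations that the document does not report. The direction does not depend on the equal-SD assumption: apart from the one degree of freedom spent on the coefficient, a fitted slope leaves no more variance than a slope forced to 1, and the gain disappears only if the true slope is 1.

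The within-arm fault is less certain because it rests on the literal reading. If it applies, it overstates the standard error by 1/√(1 − rho).

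**What to change.** Replace the t-test sentence in Statistical analyses with:

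> Between-arm differences in follow-up mean scores will be estimated by linear regression (ANCOVA) on treatment arm and the baseline value of that score, with 95 % CI; within-arm change will be described with paired estimates and confidence intervals only.

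The cost is wording and analysis code. No new data are needed, since the baseline CPQ scores are collected before allocation and used to screen for eligibility. The article reports recruitment as ongoing and places the analyses in 2017 to 2019, so the change can be made before the data are analysed. Sample size and the relative risk and risk difference analyses stay as they are.
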